## Figures and Tables

**Figure 1 nutrients-13-03472-f001:**
[figure not shown]
DUET study flow diagram that focuses on the enrollment trajectory.

**Table 1 nutrients-13-03472-t001:** DUET diet and exercise sessions.

Week	Topic/Brief Description
1	What Can You Do to Lower Your Risk of Cancer? American Institute of Cancer Research’s (AICR) dietary recommendations to lower cancer risk and why they are important.
2	Get on Track for Success! Using the Fitbit Aria weight scale each day and tracking tips and tools to promote weight loss.
3	Be Safe While Losing Weight! Importance of setting safe weekly weight loss goals that reduce the risk of sarcopenia.
4	Moving Towards Better Health Incremental goal setting to ultimately achieve 150 min of aerobic, resistance and flexibility exercises each week.
5	Let’s Get Physical and Step It Up! Use of the Fitbit wrist monitor to track physical activity and making a safe exercise plan with incremental goals
6	Be S.M.A.R.T. About Physical Activity and Exercise. How to make exercise goals specific, measurable, achievable, relevant and time-based.
7	The Sweet ‘n Low-down on Sugar and Fasting. Setting goals to limit of sugar intake and reviewing the concept and evidence for intermittent fasting.
8	Been Resisting “Resistance” Exercises? Importance of resistance exercise and instructions on how to perform them safely.
9	Yes, Portion Size Does Matter! Determining and tracking portions sizes; managing temptation while at the grocery store and dining out.
10	Why Are Bending Down and Touching Your Toes So Important for Good Health? How flexibility and balance exercises promote strength, and prevent falls and pain; instructions on how to begin safely.
11	Red and Processed Meats: How Can Something So Good Be So Bad? AICR recommendations on limiting red and processed meats. Harnessing social support to make dietary changes.
12	Did You Know that Your Surroundings Can Make You More Likely to Exercise? Managing environmental influences in support and promotion of good exercise habits.
13	Get the Skinny on Trimming the Fat. How high-fat foods contribute to risk of cancer and comorbidities; understanding different types of fat and food sources.
14	Reaping the Benefits of Whole Grains. Recommendations for whole grain daily intake and food sources.
15	Being Labeled is Not Always Bad. Importance of reading food labels and how.
16	Too pooped to Make Healthy Diet Choices? Recognizing and managing fatigue in support of healthy food preparation and making good choices.
17	Super Food Heroes: Fruits and Vegetables. Vegetables and fruits as sources of fiber, phytochemicals and antioxidants to reduce the risk for cancer and comorbidities; recommendation on sources, daily intake and serving sizes.
18	Problem Solving Strategies to Help You Get More Healthy Foods into Your Diet Identifying barriers/problems, brainstorming solutions, evaluating pros/cons, and developing an action plan.
19	Have Concerns About Pesticides Been Bugging You? Strategies to reduce pesticides in the diet and on foods; money and timesaving tips.
20	Want to Join the Party Without Blowing Your Diet? Recommendations on alcohol and cancer risk; making healthy choices when attending/hosting social gatherings.
21	Need a Break From Stress? Recognizing how stress influences physical and emotional wellbeing and strategies to manage it.
22	Why Am I Hungry All the Time? How to recognize hunger, and manage emotional or habitual eating.
23	Are Supplements Really Good for You? Information on safety and recommendations for supplement use
24	You did it! You Completed the DUET Program! Celebrating healthful eating and exercise behavior changes with positive rewards and planning for maintenance

**Table 2 nutrients-13-03472-t002:** Outcome measures.

**PRIMARY OUTCOME**
**Body Weight:** Weight is measured in light clothing without shoes. Zoom^®^ images are captured of the “zeroed” scale display, the participant actively weighing, and final images of the display showing the participant’s weight. The assessor verifies the weight with both the participant and partner. Weight is measured twice, and the average taken for analyses.
**SECONDARY OUTCOMES**
**Waist circumference:** The participant faces the camera and positions clothing to reveal midriff; as the partner is coached to encircle the waist with one of the ribbons at the level of the umbilicus [18]. As the participant rotates, the assessor checks to assure the ribbon is flat against the skin and parallel to the floor. Upon exhale, the partner uses a felt-tip marker to mark the ribbon at the point of overlap. The process is repeated with the second ribbon. Both ribbons are returned to the study office and measured in centimeters and the average taken for analyses. **Diet Quality:** A trained nutritionist conducts telephone-based dietary recalls of a non-consecutive weekday and weekend day using the National Cancer Institute (NCI)-developed Automated Self-Administered 24-h (ASA24) recall dietary assessment web-based tool (https://epi.grants.cancer.gov/asa24/, accessed on 27 September 2021). Calorie intake and nutrient density are averaged over the 2 days for each time point and Diet Quality is calculated using the Healthy Eating Index (HEI)-2015 [19]. **Physical Activity:** Programmed actigraphs (Fort Walton, FL, USA) objectively capture physical activity over a 7-day period and are then downloaded and processed using procedures and software supplied by the manufacturer and using methods similar to those we have reported previously [20,21]. Physical activity also will be measured by self-report using the Godin Leisure-Time Exercise Questionnaire, given its excellent reliability and validity with cancer survivors [22,23]. **Physical Performance Testing:** The Senior Fitness Battery assesses physical performance objectively across multiple domains, is sensitive to change, minimizes ceiling effects, and has normative scores [24]. Usually conducted in-person, tests were adapted to virtual use, refined, and then evaluated for validity and reliability [17]; arm curls and grip strength, were omitted because of excessive equipment and postage costs. - 30-s chair stand (lower body strength): A standard 18” unpadded chair is used, though if the participant does not have one, the identical chair is used for both baseline and follow-up assessments. The participant sits in view of the camera and is instructed to cross arms with hands on shoulders. Upon the assessor’s signal to start, the participant stands up and sits down as many times as possible during a 30-s timed period. - 8′ Get Up & Go (agility, dynamic balance): Participant begins seated with crossed arms and hands on shoulders while the partner places a sticker and the end of the 8′cord (from mailed supplies) beneath the toe and extends the cord fully in front of the chair. The endpoint is marked by a soccer cone and the cord removed. The camera is positioned to capture the full course with a focus on the chair (start and end points for this test). Upon the signal to start, the participant stands, walks as fast as possible (without running) around the cone, returns to the chair, and sits down. The test is timed using the video—starting from the sign of movement until seated again. - 8′ Walk (gait speed): The chair is removed, and the participant stands with their toe on the sticker (see test above). Upon the signal to start, they walk as fast as possible through the 8′point marked by 2 soccer cones (another cone is added to increase visibility of the finish line). This test also is timed using the video, starting from the sign of movement until the finish line is crossed. - Sit-and-reach (flexibility): Seated on the edge of the chair, the participant extends one leg with their heel on the floor, the knee straightened, and the toe pointed to the ceiling. The camera captures the side view, and the assessor guides the participant to overlap their hands and extend them towards the toe. The partner measures the distance from the middle finger to the big toe with a vinyl tape measure. Positive values are recorded for over-reaching, negative for under-reaching, and zero for touching. - Back scratch (flexibility): The camera captures a back view while the participant reaches over their same shoulder while at the same time reaching their other arm directly back in an attempt to their clasp hands. The partner measures the distance between the closest fingers. Positive for over-reach, negative for under-reaching, zero for touching. - 2-min step test (endurance): The partner is instructed to palpate the participant to locate their iliac crest and then uses the vinyl tape measure to record the distance to the top of the patella, which is called-out to the assessor. The assessor calculates the midpoint, which is denoted by a sticker. Then the partner is asked to measure the distance from the sticker to the floor and call-out the value to the assessor. The assessor records this value for future testing and instructs the partner to measure this distance against a wall and to mark it with another sticker. The camera captures the side view and upon the command to start, the participant is instructed to “march in place” for 2 min making sure to bring their knees up to point of the sticker. The participant is instructed not to talk, and to take breaks, and briefly reach out to the wall to regain balance as needed while timer continues (partners are instructed to “spot” the participant as needed). The assessor counts steps during the 2-min period (steps not reaching the mark are not counted). **Balance Testing:** Zoom^®^ captures side-by-side, semi-tandem and tandem stance balance testing as advocated by the Centers for Disease Control [25]. To reduce ceiling effects, the latter test is extended for up to two minutes (or until the time the stance is broken). **Circulating Biomarkers:** DBS captured on the designated card are dried thoroughly (>4 h at room temperature), then inserted into a foil pouch with desiccant and frozen (0 F^o^ or below) until analyzed. DBS eluents are batch-tested against known standards for insulin, glucose, leptin, adiponectin, high density lipoprotein (HDL) and total cholesterol, triglycerides, interleukin-6 (IL6), c-reactive protein (CRP) and tumor necrosis factor alpha (TNFα) at the University of Washington as described previously [26]. Values are expressed in plasma equivalent terms. **Quality of Life:** The PROMIS global health scale and the EuroQOL-5D-5L (EQ-5D-5L) will be used to measure QOL [27]. The EQ-5D-5L includes 5 dimensions (Mobility, Self-care, Pain/Discomfort, and Anxiety/Depression) and the scores are used to calculate Quality Adjusted Life Years. **Comorbidity:** The Older Americans Resources & Services (OARS) Comorbidity Index (43-items) will assess the number and severity of chronic medical conditions and symptoms. Since falls are a particular issue in this population, an item validated by Chen & Janke that assesses falls in the past year also will be included [28,29].

**Table 3 nutrients-13-03472-t003:** Study sample characteristics of DUET cancer survivors and partners *.

	Survivors (*n* = 56)	Partners (*n* = 56)	*p*-Value **
Cancer Diagnosis			<0.001
(*n*/%) *			
- Breast	45 (80%)	4 (7%)	
- Colorectal	1 (2%)	0	
- Gynecologic	2 (4%)	2 (4%)	
- Genitourinary	8 (14%)	1 (2%)	
Months elapsed since diagnosis			
- Mean (sd) (*n* = 53)	67.5 (72)		
- Range	10–303		
- Miles between Survivor and Partner (*n*/%)			
- 0 (cohabitate)	24 (43%)		
- Greater than 0, but less than 5	12 (21%)		
- 5 to 10	8 (14%)		
- More than 10	12 (21%)		
Race/Ethnicity			0.8
- Non-Hispanic White	35 (63%)	34 (61%)	
- Hispanic White	0	1 (2%)	
- Non-Hispanic Black	19 (34%)	21 (38%)	
- Hispanic Black	1 (2%)	0	
- Other	1 (2%)	0	
Gender (n/%)			0.03
- Male	8 (14%)	18 (32%)	
- Female	48 (86%)	38 (68%)	
Age (years)			0.1
- Mean (sd)	60.3 (11)	56.5 (14.3)	
- Range	32 79	23 81	
Educational Status			0.9
- High School Graduate	7 (13%)	9 (16%)	
- Some College/Junior College/Trade School	18 (32%)	17 (30%)	
- College Graduate/Post Graduate	30 (54%)	29 (52%)	
- Unknown	1 (2%)	1 (2%)	
Income			0.5
- Less than $50k/year	11 (20%)	7 (13%)	
- $50k/year or more	24 (43%)	23 (41%)	
- Unreported or Refused/Unknown	21 (38%)	26 (46%)	
Rural (*n*/%)	4 (7%)	5 (9%)	1
BMI (kg/m^2^) Mean (sd)	31.8 (5.8)	32.9 (6.1)	0.3
Employment (*n*/%)			1
- Employed	31 (55%)	31 (55%)	
- Retired	18 (32%)	18 (32%)	
- Other	7 (13%)	7 (13%)	

* Information on cancer-type was verified for cancer survivors, but was self-reported for supportive partners. ** For cancer diagnosis, participants with cancer were compared to participants without cancer; for race/ethnicity, only Non-Hispanic Whites and Non-Hispanic Blacks were compared; for educational status, participants with a response of unknown were excluded from the analysis.

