## 2. Materials and Methods

### 2.1. Overall Design

DUET is a single-blinded, 2-arm randomized controlled trial (RCT) that will test a 6-month, web-based lifestyle intervention against a wait-list control among 56 dyads. Each dyad is comprised of a survivor of an obesity-related early-stage cancer and their supportive partner, both of whom have obesity or overweight, are insufficiently active, and consume suboptimal diets. The main outcome (body weight) is assessed at baseline and 6 months, along with several other secondary outcomes. This trial was approved by the University of Alabama at Birmingham (UAB) Institutional Review Board (300003882/Approval date: 10-28-2019) and registered with ClinicalTrials.gov (NCT04132219).

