The website includes the following sections: My Profile, Healthy Weight, Healthy Eating, Exercise, Weekly Sessions, Tools, News You Can Use, and Team Support. All users are given instructions on using the website features and encouraged to call the research team with any problems or questions. Once logged in, participants can update personal information (gender, age, height, weight, diet, physical activity, and cancer history) in the My Profile feature and then access tailored content in the Healthy Weight, Healthy Eating, and Exercise sections. Participants pursue and track their weight, diet, and exercise using study-provided equipment (Fitbit^®^ Aria 2 digital scales and Inspire fitness trackers (San Francisco, CA, USA), Portion Doctor^®^ tableware (Portion Health Products, St. Augustine Beach, FL, USA) and exercise bands (Theraband Academy, Akron, OH, USA)). Dyads also are encouraged to work as a team and use the commercially available MyFitnessPal (https://www.myfitnesspal.com/, accessed on 27 September 2021) app to set goals and view progress; log-ins and data are tracked to assess adherence. Participants are cued via text messages to complete 24 weekly interactive diet and exercise modules in the Sessions section; sessions range from 10–20 min. See Table 1 for session topics.

The Tools section includes tracking forms, online calculators, planning guides, tip sheets, and other healthy eating and exercise resources. Summarized updates on recent findings from salient research on diet, exercise, and/or weight loss for cancer prevention and control is provided in the News feature. The Team Support page offers practical tips on how dyads can support each other to promote lifestyle change (e.g., active listening). Regular website usage is encouraged via text messages (three per week) and tracked to assess intervention adherence. Short Message System (SMS) Text Messages also are a key component of the DUET intervention. After an initial welcome message, text messages are delivered at a frequency of three per week over the course of the intervention for a total of 72 messages for intervention.

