### 2.5. Assessments

Baseline and 6-month follow-up assessments are largely identical except that some demographic and health characteristics that are likely to be time invariant for an adult sample over the study period (e.g., race/ethnicity, marital and educational status, height) are self-reported only at enrollment. Originally designed to include home-based assessments, the DUET protocol was modified prior to recruitment to virtual assessments via Zoom^®^ (San Jose, CA, USA) in order to continue research activities during the COVID-19 pandemic. Assessors were trained and evaluated for accuracy prior to initiation; measures were evaluated for reliability, as well as validity with those collected in-person data that are featured in a separate report [17]. All Zoom^®^ sessions are recorded to increase accuracy for timed performance testing to reduce discrepancies resulting from variable transmission of sight and sound and allow for periodic quality assurance evaluations among assessors. Once assessors review these files, time the tests, log the data, and quality assurance tests are completed, the recordings are deleted. Virtual assessments are scheduled during times when both dyad members can participate and occur in tandem with one member of the dyad undergoing the assessment first and the other recording the encounter on Zoom^®^, and then vice versa. Dyads are asked to prepare by viewing videos on performance testing (https://youtu.be/lbxctNuOgLk, accessed on 27 September 2021) and dried blood spot (DBS) collection (https://youtu.be/lBPLS4PoHv4, accessed on 27 September 2021).

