Upon completion of the intervention both dyad members undergo separate telephone debriefings on the acceptability and satisfaction of the various intervention components (e.g., website, equipment, text messages) and their suggestions for improvement are solicited.

As with any lifestyle intervention trial conducted in a high-risk patient population, especially one that is home-based and unsupervised, adverse events are a key concern. Thus, changes in health status of both study arms are systematically ascertained at study midpoint (3 months), in addition to 6-month follow-up. Any hospitalizations are logged, and admittance to the hospital resulting in an overnight stay, as well as events that are permanently disabling or life threatening are categorized as “serious” with attribution of the intervention explored further. Furthermore, all study participants are encouraged to call a toll-free study number to report any adverse events that occur between assessments.

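### The presumed assessor blind is at risk at the 6-month video visit, where arm-specific devices can be on camera while performance tests are scored by judgement

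*Protocol article*

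**What the plan says.** **Blinding.** Section 2.1 states: "DUET is a single-blinded, 2-arm randomized controlled trial (RCT". Neither the abstract nor the methods say which party is blinded.

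**Devices.** Section 2.4 lists "Aria 2 digital scales and Inspire fitness trackers" among the equipment supplied with the intervention. Table 1 confirms where the tracker is worn (week 5: "Use of the Fitbit wrist monitor to track physical activity"), and its week 2 session promotes daily use of the Aria scale. Under section 2.3, wait-list dyads receive the intervention only after their 6-month assessments.

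**The visit.** Section 2.5 describes a recorded Zoom session with both dyad members present, one being assessed while the other handles the recording. In Table 2 the chair stand reads: "The participant sits in view of the camera and is instructed to cross arms with hands on shoulders". The Get Up & Go starts from the same posture. For weight, images are taken of the scale display and of the participant on the scale.

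**Scoring.** For the step test, "The assessor counts steps during the 2-min period (steps not reaching the mark are not counted". The Get Up & Go and the 8-foot walk are timed from the video, starting when movement is first seen. The tandem stance runs for up to two minutes or until it is broken. On the files, section 2.5 says: "Once assessors review these files, time the tests, log the data, and quality assurance tests are completed, the recordings are deleted".

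**Debriefing.** Section 2.5 adds: "Upon completion of the intervention both dyad members undergo separate telephone debriefings". It does not say who makes the call or whether it comes before or after the 6-month assessment.

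**The concern.** Participants in a wait-list design know whether they have had the programme. A single blind can therefore protect outcome collection only through the assessor. At 6 months the study's own equipment separates the arms, the assessment positions place wrists and scale before the camera, and several tests turn on a human call: whether a knee reached the mark, when movement began, when a stance broke.

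An assessor who recognises the arm may encourage more warmly or score more leniently in one arm. Baseline assessments precede randomization (section 2.3), so they cannot be biased by arm in this way. Any such effect would enter at 6 months only and pass straight into the between-arm comparison of change. The introduction includes physical functioning and performance among the outcomes expected to improve under DUET.

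**Working it through.** The article gives no figure for blinding or for scoring error, so there is none to reproduce on this point. Its power statement concerns weight and has no bearing here.

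**Step 1: is there an arm-specific cue?** The tracker and the Aria scale come with the intervention (section 2.4). Controls get the intervention after the 6-month assessment (section 2.3). At that visit, study-issued devices therefore belong to the intervention arm. The tracker is the clearer cue. The scale is less clear, because section 2.5 says that a digital scale is sent to anyone without one and does not say which scale is used at 6 months.

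**Step 2: can the assessor see it?** Crossed arms with hands on shoulders are in view for the chair stand and the Get Up & Go. The partner is also active in the session, measuring and spotting. The dyad is the randomized unit, so a tracker on either member can reveal both.

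**Step 3: does the person who may see it also score?** For the step test, yes: in Table 2 the assessor instructs, records the step height and counts the valid steps. For the timed tests, section 2.5 says only that assessors, in the plural, review the files and time them.

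**Step 4: is there a described step against arm-dependent scoring?** Section 2.5 describes training, accuracy checks, reliability and validity evaluation, recording and periodic quality assurance. None is said to be masked to arm.

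**Step 5: illustrative size.** Only the number of dyads per arm (28, section 2.6) comes from the article. The rest are assumptions.

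- Intervention members: 28 dyads × 2 = 56.
- Members revealed, assuming 50% to 90%: 0.5 × 56 = 28; 0.9 × 56 = 50.4, about 50.
- Steps misjudged per revealed member, assuming 80 counted steps and 3% to 5% all misjudged in one direction: 80 × 0.03 = 2.4; 80 × 0.05 = 4.0.
- Shift in the arm mean = share revealed × steps misjudged: 0.5 × 2.4 = 1.2; 0.9 × 4.0 = 3.6.

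The step-test difference would shift by about 1 to 4 steps.

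A variant takes 50% to 90% as the chance that each member wears the tracker, independently of the other, and lets one tracker reveal both. The share revealed is then 1 − (1 − p)²: 1 − 0.5² = 0.75 and 1 − 0.1² = 0.99. The shift is 0.75 × 2.4 = 1.8 to 0.99 × 4.0 = 3.96 steps, inside the same range.

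The article gives no standard deviation for the step test, so the shift cannot be turned into a standardized effect or an error rate.

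**The case against.** The strongest reply is that this rests partly on silence. An article condenses the full protocol, and visit scripts, staff allocation and file handling commonly sit in that protocol or in a manual. That stands: the absence of a masking instruction here is not in itself an error. What remains is the workflow the article does describe, which puts an arm-specific cue and a judgement-based count before the same person.

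Four stronger readings are tempting, and the article does not support them.

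- **That the blind cannot hold.** Nothing says that trackers are worn during the visit, and a control could own a similar device. The blind is at risk; it is not shown to fail. That assessors are the blinded party is itself an inference.
- **That each assessor times their own session.** The plural in section 2.5 is equally compatible with cross-review. Only the step count is tied to the assessor directing the test.
- **That the debriefing unblinds assessors.** This would need the call to come before the assessment and the assessor to make it or hear of it. Neither is stated.
- **That the primary outcome is compromised.** Weight is read from an imaged display, verified with both members, measured twice and averaged, which leaves little room for judgement.

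The safeguards in section 2.5 also count: training, recording and quality assurance limit general scoring error, and deletion follows quality assurance. They do not specifically address scoring that differs by arm. Finally, section 2.6 makes every analysis other than weight loss exploratory, which lowers the stakes.

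**Conclusion.** The point holds as a risk of modest priority. If assessors are the blinded party, the described 6-month visit leaves that blind open to a visible arm-specific cue on tests that depend on judgement: the step test most directly, then the timed walk, Get Up & Go, chair stand and balance.

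An illustrative size is about 1 to 4 steps on the step test. That rests wholly on assumed values for the share revealed (50% to 90%), the error (3% to 5%, all in one direction) and the count (about 80 steps). The conclusion about weight loss is not called into question. Action is worthwhile because the change is small and because masked rescoring is impossible once a recording is gone.

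**What to change.** 1. In the existing preparation material, for both arms: ask participants to remove any wrist tracker for the video session, keep programme materials out of view and not mention their arm.
2. Have step counts, timings and stance breaks scored from the existing recording by a member of the current assessor team who did not run that session and is not told arm or visit. Delete the recording only after that. This depends on item 1, since a tracker in the frame would reach the second scorer too. Where a baseline recording has already been deleted, masking to visit is lost, but the 6-month file can still be scored masked to arm.
3. Hold the debriefing call after the 6-month assessment is complete.
4. State who is blinded.

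The cost is some preparation wording, a swap of who reviews which file, slightly longer file retention and some scheduling. The Results section says that data collection had up to about five months to run, so the change could reach the remaining visits and any recordings still held.
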